#### 3.2.2. Biological Samples

To be able to identify biological changes in intestinal inflammation levels, faecal samples for analysis of faecal calprotectin (the gold standard of intestinal inflammation) [50], will be taken from both groups at baseline, and after the 6-week treatment period. Microbiota communities in the gut will also be measured from stool samples to determine changes in the communities. The methods will utilise 16S rRNA gene technology, where sequencing will be completed on Illumina MiSeq for targeted amplicon sequencing and NextSeq for untargeted bacteriophage sequencing. The method will allow the exploration of associations between gut communities, calprotectin, and other metadata. In brief for bacterial community sequencing, raw, paired-end .fastq sequencing files are quality filtered (phred > Q30), merged, trimmed, and clustered in to OTUs (operational taxonomics units) at 97% similarity. Chimeric and non-bacterial reads are removed before taxonomic assignment by alignment to the SILVA or Greengenes databases. Taxonomic classifications are merged at the genus level. Taxonomic abundances are normalized via rarefaction or conversion to proportional abundances. Mean alpha diversity measures, including taxonomic richness and Shannon diversity, are compared between cohorts using generalized linear mixed models. Weighted Bray–Curtis dissimilarity is the measure of beta diversity employed to assess dissimilarities in community structure between cohorts using PERMANOVA. Differential bacterial taxa between cohorts are identified using Maaslin2. Where multiple pairwise comparisons are made, suitable multiple-hypothesis correction is applied.

For untargeted sequencing of the phage fraction on the Illumina NovaSeq. Raw, paired-end .fastq sequences are filtered for quality (phred > Q30), length, (>100 n) and reads aligning to human genomes. Contiguous sequences are assembled before filtering based on read mapping and confirmation of viral origin. Taxonomic assignment at the species level is performed by alignment to relevant viral databases (NCBI, GPD, etc.) Analyses of alpha and beta diversity as well as differential taxa identification are performed as per bacterial community methods. Bacterial and viral communities are normalised via cumulative sum scaling and centered log ratio transformation before MixOmics is used to identify co-abundant features of bacterial and bacteriophage communities associated with cohort membership or intervention group.

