### 3.2. Data Collection

All measurements will be made inside the Physiology laboratory at the University of Hertfordshire and will be carried out in the exact same way on two occasions: at baseline and after six weeks.

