### 3.4. Statistical Analysis

Continuous experimental variables will be presented as mean values along with their corresponding standard deviations. To compare participant characteristics at baseline, as well as compliance levels, experimental anthocyanin intake, experimental energy intake, and experimental sugars (g/day) between the trial arms, between-group linear mixed effects models will be utilized. In these models, the group will be treated as a fixed factor, and random intercepts will be included for participants.

All analyses of the intervention-based data will follow an intention-to-treat approach. To determine the effects of the intervention on all of the outcome measures, differences in the changes from baseline to 6 weeks between the two trial arms will be examined using linear mixed-effects models with a group modelled as a fixed factor and random intercepts by participants adopted. For linear mixed models, the mean difference between groups in changes from baseline to 6 weeks (*b*) and 95% confidence intervals of the difference will be presented. Effect sizes were calculated for the changes from baseline to 6 weeks between the two groups, using Cohen’s *d*, in accordance with McGough & Faraone [51]. Cohen’s d values will be interpreted as 0.2 = small, 0.5 = medium, and 0.8 = large [52]. The efficacy of blinding will be assessed using a one-way chi-square (*Χ*^2^) goodness-of-fit test. Chi-square analyses will be calculated using Monte-Carlo simulation to determine probability values. All statistical analyses will be performed using SPSS v28 (IBM Inc., SPSS, Chicago, IL, USA), and statistical significance will be considered at a *p* ≤ 0.05 level.

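### The microbiome and phage analyses are stated as between-cohort comparisons with no visit or baseline term, which does not match the paired samples, the stated aim of detecting change, or the contrast set in Section 3.4

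*Protocol article*

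**What the plan says.** Section 3.2 of the protocol article says that all measurements "will be carried out in the exact same way on two occasions: at baseline and after six weeks". In Section 3.2.2 the faecal samples for calprotectin "will be taken from both groups at baseline, and after the 6-week treatment period", and the microbiome aim follows: "Microbiota communities in the gut will also be measured from stool samples to determine changes in the communities". The design is therefore two stool samples per participant, and the question is one of change.

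The same section then names three bacterial analyses, each with the same contrast:

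- Alpha-diversity measures "are compared between cohorts using generalized linear mixed models".
- The Bray–Curtis measure of beta diversity is "employed to assess dissimilarities in community structure between cohorts using PERMANOVA".
- For individual taxa the text reads: "Differential bacterial taxa between cohorts are identified using Maaslin2".

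The phage analyses are to follow the bacterial methods. The joint bacterial and phage analysis looks for features "associated with cohort membership or intervention group", which sets cohort beside trial arm as though the two might differ. *Cohort* is not defined anywhere. None of these analyses names a visit term, an arm-by-visit contrast, a baseline covariate or a restriction on the permutations.

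Section 3.4 gives the general rule, which covers every outcome: "differences in the changes from baseline to 6 weeks between the two trial arms will be examined". The tool it names is a mixed model with a random intercept per participant.

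**The concern.** The contrast that Section 3.2.2 states is not the one its own aim requires, nor the one Section 3.4 prescribes. Section 4 adds to the mismatch. It predicts that the supplement will modulate the stability of the gut microbiome relative to placebo, and stability is a within-person quantity over time.

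An analyst who follows Section 3.2.2 to the letter has two samples per person, one grouping factor and no instruction about pairing. Depending on the choices then made, a PERMANOVA or Maaslin2 result could reflect stable differences between people that were present at baseline, or a real 6-week shift could be diluted, or collected baseline information could go unused.

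**Working it through.** **Inputs from the documents.** Two samples per participant (Sections 3.2 and 3.2.2). Twenty per arm with 20% expected attrition, hence 20 × 0.8 = 16 per arm evaluable (Section 2.4). Significance at p ≤ 0.05 (Section 3.4), taken as two-sided. The plan gives no figure for the microbiome analyses, so there is none to reproduce.

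**Assumptions.** The within-person correlation ρ is not in the documents and is varied from 0 to 0.9. The abundance model and effect sizes below are illustrative.

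**1. Type I error for a single measure if both visits are pooled and pairing is ignored.** The true variance of an arm mean over 2n samples is (1 + ρ) times the value assumed under independence, so

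α = 2 × [1 − Φ(1.96 / √(1 + ρ))].

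This gives 8.6%, 11.0%, 13.3% and 15.5% at ρ = 0.3, 0.5, 0.7 and 0.9.

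**2. Type I error for PERMANOVA.** Null simulation with 40 log-normal taxa, Bray–Curtis distances, 1000 trials per setting and 199 permutations. Monte Carlo standard error near 5% is √(0.05 × 0.95 / 1000) = 0.7 points. Rejection rates are in %, for 16 / 20 per arm:

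| ρ | Both visits, free permutation | Both visits, participants permuted as units | Week 6 only |
|---|---|---|---|
| 0 | 4.4 / 5.0 | 3.6 / 4.6 | 5.0 / 6.4 |
| 0.3 | 16.9 / 14.1 | 5.4 / 4.2 | 4.9 / 4.9 |
| 0.5 | 21.7 / 18.3 | 4.0 / 4.8 | 5.8 / 4.9 |
| 0.7 | 36.2 / 35.2 | 5.8 / 4.5 | 5.6 / 4.6 |
| 0.9 | 41.6 / 40.3 | 6.7 / 3.9 | 6.0 / 4.5 |

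Only the first column fails. The other two hold the level.

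**3. Power of the valid options for a single measure.** Randomisation makes the true baseline difference zero. If the week-6 effect is d, a group effect averaged over both visits is therefore (0 + d) / 2 = d/2. Power is Φ(δ / (s√(2/n)) − 1.96) with n = 16, so √(2/16) = 0.354, and an assumed d = 0.8 SD:

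| Analysis | δ | s | ρ = 0.3 | ρ = 0.5 | ρ = 0.7 |
|---|---|---|---|---|---|
| Average of both visits | 0.4 | √((1 + ρ)/2) | 29% | 26% | 23% |
| Week 6 only | 0.8 | 1 | 62% | 62% | 62% |
| Change score | 0.8 | √(2(1 − ρ)) | 48% | 62% | 83% |
| Week 6 adjusted for baseline | 0.8 | √(1 − ρ²) | 66% | 74% | 89% |

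Example: averaging at ρ = 0.5 gives 0.4 / (0.866 × 0.354) = 1.31, and Φ(1.31 − 1.96) = 26%.

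**4. Arm-by-visit PERMANOVA.** In a second simulation (60 genera, 16 per arm), the arm-by-visit test rejected a true null in 5 to 6% of trials. With an assumed shift of 0.6 log units in 10 genera, its power was 18%, 23% and 45% at ρ = 0.5, 0.7 and 0.85. Week 6 only gave 16 to 18%, and the pooled main effect 6 to 9%. The sizes depend heavily on the assumed abundance profile, so only the pattern should be carried over.

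**The case against.** The tempting stronger reading is that the microbiome tests, as planned, inflate false positives. The documents do not support that. Nowhere does the article say that both visits are pooled, that samples are permuted freely, or that baseline is dropped. The bacterial methods are introduced as a brief summary. An arm-by-visit PERMANOVA with restricted permutation, or a Maaslin2 model with a participant random effect, is neither stated nor excluded. Model terms of that kind are commonly left to a full protocol or analysis plan.

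Section 3.4 can also be read as supplying the contrast while Section 3.2.2 supplies the tools, since a univariate mixed model cannot be fitted to a distance matrix. The mention of multiple pairwise comparisons leaves room for arm-by-visit cells.

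Much of this stands:

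- Error inflation is conditional on one particular implementation.
- The alpha-diversity analysis is already a mixed model and can carry a participant effect. Its only defect is the missing change contrast.
- Week 6 alone is unbiased in a randomised comparison, so ignoring baseline there costs precision, not validity.
- The magnitudes rest on correlations and abundance profiles that the documents do not give.

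What does not stand is that this is only omitted detail. The article states a contrast for every named test, and that contrast is not change. An analysis plan that followed Section 3.2.2 literally would inherit the mismatch, and one that followed Section 3.4 would depart from Section 3.2.2.

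**Conclusion.** The point holds as a mismatch of contrast. Section 3.2.2 states between-cohort comparisons, with cohort undefined and no visit or baseline term. The sampling is paired, the aim is change, and Section 3.4 prescribes the between-arm difference in change.

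The size depends on implementation. At worst, if both visits enter PERMANOVA with free permutation, type I error is roughly 14 to 42% for assumed ρ of 0.3 to 0.9. If participants are permuted as units, the level holds but the effect is halved: 23 to 29% power in the single-measure example, for ρ of 0.3 to 0.7. If only week 6 is used, the test is valid at 62% power, against 66 to 89% with baseline adjustment over the same range. Those powers assume a 0.8 SD effect and 16 per arm.

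Microbiome outcomes are secondary and the primary quality-of-life outcome is untouched. This is a low-severity, cheap improvement.

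**What to change.** In Section 3.2.2:

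- Define cohort as trial arm, or use trial arm throughout.
- For alpha diversity and Maaslin2, test arm-by-visit with a participant random effect, or the 6-week value adjusted for baseline.
- For PERMANOVA, test arm-by-visit with arm labels permuted across participants and each participant's two samples kept together, or analyse within-participant change with arm labels permuted across participants. Shuffling samples only within participants would not serve to test arm, because arm does not vary within a person.
- Apply the same contrast to the phage data and to the joint bacterial and phage analysis.

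The cost is a few sentences of analysis wording, with no new samples or visits. One trade-off should be known in advance: a pure change-score test can lose some power against week 6 alone if the within-person correlation is below about 0.5 (48% against 62% at ρ = 0.3 in the example). Baseline adjustment avoids that loss.

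### Phage Shannon and Bray-Curtis borrow 16S normalisation that leaves genome length in the abundances (minor, exploratory outcome)

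*Protocol article*

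**What the plan says.** All of this is in the protocol article, section 3.2.2 (Biological Samples).

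- **Two kinds of sequencing.** The plan says "sequencing will be completed on Illumina MiSeq for targeted amplicon sequencing and NextSeq for untargeted bacteriophage sequencing". The phage paragraph names a different instrument ("For untargeted sequencing of the phage fraction on the Illumina NovaSeq") but agrees that the phage reads are untargeted.
- **Bacterial methods.** 16S reads are clustered into OTUs, and then "Taxonomic abundances are normalized via rarefaction or conversion to proportional abundances". For alpha diversity: "Mean alpha diversity measures, including taxonomic richness and Shannon diversity, are compared between cohorts using generalized linear mixed models". For beta diversity: "Weighted Bray–Curtis dissimilarity is the measure of beta diversity employed to assess dissimilarities in community structure between cohorts using PERMANOVA".
- **Phage methods.** After quality filtering, "Contiguous sequences are assembled before filtering based on read mapping and confirmation of viral origin". Species are then assigned against viral databases. For the diversity step: "Analyses of alpha and beta diversity as well as differential taxa identification are performed as per bacterial community methods".
- **The only other phage normalisation stated.** "Bacterial and viral communities are normalised via cumulative sum scaling and centered log ratio transformation before MixOmics is used" belongs to the joint bacteria–phage analysis.

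No adjustment for genome or contig length appears anywhere.

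**The concern.** A 16S amplicon yields one fragment of roughly fixed length per gene copy, so a taxon's share of reads does not depend on how long its genome is. Untargeted reads are drawn from along the whole genome, so a long-genome phage yields more reads than a short-genome phage present in the same number of copies. Rarefaction and proportions equalise library size between samples. They do nothing about a factor that differs between taxa within a sample.

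If the cross-reference is followed literally, phage Shannon and weighted Bray-Curtis describe something close to the distribution of sequenced DNA, with long genomes weighted up. At stake are the size of a between-arm difference, the power to see it and, for Shannon, its direction. Section 4 (Expected Results) predicts modulation of the gut microbiome relative to placebo, so direction and size will be interpreted.

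**Working it through.** The plan gives no figure on this point, so there is nothing to reproduce.

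**Inputs.** From the document: untargeted phage reads; rarefaction or proportions; Shannon; weighted Bray-Curtis. Assumed: genome lengths, shown as a range from near-equal to 40-fold different.

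**Formulas.** For copy share g and length L of each phage:
- read share p_i = g_i L_i / Σ g_j L_j
- Shannon H = −Σ p ln p
- Bray-Curtis on proportions = ½ Σ |p_i − q_i|

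**Step 1: equal copies of two phages.** Copy-based H = ln 2 = 0.69. With 5 and 100 kb the read shares are 5/105 = 4.8% and 100/105 = 95.2%, so H = 0.19. With 5/40 kb H = 0.35, and with 5/200 kb H = 0.11.

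**Step 2: copies move from 50:50 to 80:20.** The copy-based change in H is 0.500 − 0.693 = −0.193, and Bray-Curtis is 0.300.

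| Lengths (kb) | H on reads, before → after | Change in H | Bray-Curtis on reads |
|---|---|---|---|
| 5, 5 | 0.693 → 0.500 | −0.193 | 0.300 |
| 40, 50 | 0.687 → 0.549 | −0.138 | 0.317 |
| 5, 20 | 0.500 → 0.693 | +0.193 | 0.300 |
| 5, 50 | 0.305 → 0.598 | +0.294 | 0.195 |
| 5, 100 | 0.191 → 0.451 | +0.259 | 0.119 |

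Dividing reads by length returns −0.193 and 0.300 in every row. A four-fold length ratio reverses Shannon for this shift; 40 against 50 kb does not.

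**Step 3: Bray-Curtis can move either way (5 and 100 kb).**
- Copies 99:1 against 90:10: 0.09 on copies. Read shares are 495:100 (83.2%) against 450:1000 (31.0%), giving 0.52.
- Copies 50:50 against 10:90: 0.40 on copies, 0.04 on reads.

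**Step 4: how often Shannon changes sign.** Simulation of 5000 pairs of 30-taxon communities, with lognormal abundances (log-SD 1.5), lognormal shifts (log-SD 1) and log-uniform lengths unrelated to abundance.

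| Lengths (kb) | Opposite sign, all pairs | Opposite sign, copy-based change above 0.2 in size | SD of Bray-Curtis error |
|---|---|---|---|
| equal | 0% | 0% | 0 |
| 30–60 | 5.3% | 0.1% | 0.016 |
| 5–100 | 18.8% | 9.0% | 0.060 |
| 5–200 | 23.1% | 14.2% | 0.070 |

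**Step 5: no difference between arms.** With 20 v 20, lengths of 5–200 kb, the same composition in both arms and a t-test on read-based Shannon (2000 repeats), the rejection rate was 0.050.

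**Step 6: single taxa.** Three phages with copy shares 0.5, 0.3, 0.2 moving to 0.2, 0.3, 0.5, and lengths 5, 50, 100 kb. Mean length goes from 2.5 + 15 + 20 = 37.5 to 1 + 15 + 50 = 66 kb. Every log fold change in read proportions is shifted by the same ln(37.5/66) = −0.565. Differences on the centred log-ratio scale are identical with and without length, because each taxon's own length cancels.

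**The case against.** **The unit is not stated.** The article is condensed, and it presents the sequencing pipeline as a brief account. It does not say whether phage abundance is a raw count, coverage or reads per kilobase; read mapping is mentioned only as a basis for filtering contigs. The cross-reference could mean only the indices and tests, since the phage paragraph has its own assembly and species assignment. Proportions could be taken of length-corrected coverage, so the text permits the remedy. This part stands: a reader might infer that raw counts are certain to be used, and the document does not establish that. But the text names a method for this step, that method contains no length correction, and one of its two options, rarefaction, works on counts. Where another normalisation is intended, the text says so, and only for the joint analysis.

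**False positives.** A reader might infer that length weighting manufactures treatment effects. It does not: if the arms share the same phage composition, their read shares share the same distribution too, and step 5 shows the nominal rate. What can happen is narrower. If composition does change, read-based Shannon can move when copy-based Shannon does not. For copies going from 80:20 to 20:80 with 5 and 100 kb, copy-based H stays at 0.50 and read-based H goes from 0.45 to 0.07.

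**Sign reversal in general.** A reader might also infer that all the phage diversity outcomes can reverse. Bray-Curtis has no sign, and richness is affected only through detection. The two-phage examples are extreme by design; step 4 is much milder, and with 30–60 kb reversal of a sizeable Shannon change is rare (0.1%).

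**Estimand.** Treating copy-based diversity as the target is a choice, and 16S reads count gene copies, not organisms. That is fair, but the plan gives no reason for wanting length-weighted phage diversity.

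**Conclusion.** The point holds in a limited form. Followed as written, the cross-reference gives phage Shannon and weighted Bray-Curtis values that carry a genome-length weight. The size of both measures, and their power, can be distorted; the loss of power was not quantified. Direction can be wrong for Shannon only, and to a material extent only when genome lengths differ widely: in simulation, opposite sign in 5.3% of pairs at 30–60 kb, 18.8% at 5–100 kb and 23.1% at 5–200 kb. These figures rest on assumed lengths and abundance distributions.

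False-positive control under identical phage composition, richness apart from detection, and log-ratio contrasts of single taxa are not at issue. An unreported length correction cannot be excluded. The outcome is secondary and exploratory, so this is a minor point that leaves the quality-of-life primary outcome and the planned N of 40 as they are.

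**What to change.** In the phage paragraph of section 3.2.2, state that mapped phage reads are divided by the length of the contig or genome to which they map (reads per kilobase, or coverage) and rescaled to proportions within each sample before Shannon, Bray-Curtis and PERMANOVA are computed. The models and tests that follow stay the same. Count-based rarefaction would then be used for phage richness only.

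The cost is one sentence and one extra pipeline step, with no new samples or sequencing. If a length correction is already part of the laboratory's pipeline, saying so closes the point.

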#### 3.2.3. Blood Samples

Venous hematological samples will be collected from the antecubital vein (12 mL) directly into uncoated blood collection tubes (Fisher Scientific, Pittsburgh, PA, USA). Blood will be allowed to clot for 30 min before serum separation by centrifugation at 1000× *g*. Serum will be aliquoted and stored at −80 degrees C until assayed. We will use a multiplex approach and develop a bespoke panel (BioLegend Legend Plex) to enable measurement of pro-inflammatory and anti-inflammatory cytokines TNF-a, IL-6, IL-17A, IL-12/IL-23 and anti-inflammatory cytokines IL-10, TGF-beta using a BD FACS CANTO II flow cytometer according to the Legend Plex set up instructions.

### 3.3. Data Management

The Data Protection Act of 2018’s standard guidelines will be followed in the data-gathering and storage processes. Electronic spreadsheets will be used to input data, and Microsoft OneDrive will be used to store them on a secure university server. All information will be handled in confidence and made anonymous for analysis. For the length of the study, hard copies of the data and documents will be stored in a locked filing cabinet. Data will be transmitted to the University of Central Lancashire Research Data Archive (CLOK) after the study is finished, where they will be stored for 7 years. After this time, hard copies will be confidentially disposed of, and electronic data will be erased.

### 3.4. Statistical Analysis

Continuous experimental variables will be presented as mean values along with their corresponding standard deviations. To compare participant characteristics at baseline, as well as compliance levels, experimental anthocyanin intake, experimental energy intake, and experimental sugars (g/day) between the trial arms, between-group linear mixed effects models will be utilized. In these models, the group will be treated as a fixed factor, and random intercepts will be included for participants.

All analyses of the intervention-based data will follow an intention-to-treat approach. To determine the effects of the intervention on all of the outcome measures, differences in the changes from baseline to 6 weeks between the two trial arms will be examined using linear mixed-effects models with a group modelled as a fixed factor and random intercepts by participants adopted. For linear mixed models, the mean difference between groups in changes from baseline to 6 weeks (*b*) and 95% confidence intervals of the difference will be presented. Effect sizes were calculated for the changes from baseline to 6 weeks between the two groups, using Cohen’s *d*, in accordance with McGough & Faraone [51]. Cohen’s d values will be interpreted as 0.2 = small, 0.5 = medium, and 0.8 = large [52]. The efficacy of blinding will be assessed using a one-way chi-square (*Χ*^2^) goodness-of-fit test. Chi-square analyses will be calculated using Monte-Carlo simulation to determine probability values. All statistical analyses will be performed using SPSS v28 (IBM Inc., SPSS, Chicago, IL, USA), and statistical significance will be considered at a *p* ≤ 0.05 level.

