## 2. Experimental Design

### 2.1. Study Design and Setting

This study adheres to the latest guidelines for reporting parallel-group randomized trials [32]. The University of Hertfordshire in Hertfordshire, South England, will serve as the location for the trial. The research follows a 6-week parallel design, incorporating randomized allocation with a placebo control (Figure 1). Upon confirming a participant’s suitability and enrollment, a computer program (random assignment software) will individually assign them to one of two groups for the duration of 6 weeks: (1) Montmorency tart cherry supplement or (2) placebo. The primary and secondary outcome variables will be assessed at baseline and after 6 weeks, as described below. Consistent with previous studies on UC management, the primary outcome will be on examining the differences between groups in the Inflammatory Bowel Disease Quality of Life Questionnaire questionnaire between the two groups. Secondary outcomes will be other health-related questionnaires and biological indices.

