### 2.2. Inclusion Criteria

To be eligible for inclusion in this study, participants must meet the following criteria: (1) have a confirmed diagnosis of UC for a minimum of 6 months, (2) exhibit mild to moderate disease activity at the time of enrollment, (3) fall within the age range of 18 to 65 years, and (4) have maintained consistent use of medication for a minimum of 3 months. The aforementioned inclusion criteria were collectively adopted based on previous randomized trials in patients with UC [33,34]. Mild–moderate disease activity will be given a Mayo Clinic Score between 3–10, in accordance with the British Society of Gastroenterology consensus guidelines [35].

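### The comparison of raw changes without a baseline covariate is valid but generally less precise than a baseline-adjusted analysis, and the baseline values are already collected

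*Protocol article*

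**What the plan says.** Section 3.4 (Statistical Analysis) fixes one model for the intervention data. Its stated scope is "To determine the effects of the intervention on all of the outcome measures". The outcome form is given as "differences in the changes from baseline to 6 weeks between the two trial arms will be examined", the method is a linear mixed-effects model, and the model terms are given as "with a group modelled as a fixed factor and random intercepts by participants adopted". The effect to be reported is "the mean difference between groups in changes from baseline to 6 weeks (*b*) and 95% confidence intervals of the difference will be presented". No baseline value or other covariate is named.

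Section 2.1 confirms that the covariate will exist: "The primary and secondary outcome variables will be assessed at baseline and after 6 weeks, as described below".

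Section 3.4 also plans between-group models for baseline variables ("To compare participant characteristics at baseline"). Section 2.4 sizes the trial on change scores: 20 per arm, 20% attrition and a 6.5-point difference, with no standard deviation stated.

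**The concern.** A change score removes the baseline value with a slope fixed at 1. The regression of week 6 on baseline usually has a slope below 1, so the change score subtracts too much of the baseline. Two things follow in a trial of this size. The estimate has more variance than it needs. And if one arm happens to start worse, regression to the mean makes that arm look as if it improved more.

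The mixed-model label does not repair this. With one change score per participant, a random participant intercept cannot be separated from the residual, so the model reduces to a two-sample comparison of mean changes. Modelling baseline differences between the arms does not repair it either. Under randomisation such a test examines a null hypothesis already known to be true, and its result does not enter the treatment estimate.

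**Working it through.** **Inputs from the article.** Section 2.4 gives 20 per arm, 20% attrition, α of 5% and a 6.5-point difference. The value 0.80 is labelled β there and is read here as power. Evaluable participants: 20 × 0.8 = 16 per arm.

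**Assumptions.** The test is two-sided. The change-score analysis has exactly 80% power with 16 per arm. The correlation ρ is not in the article and is varied.

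**The plan's own figure.** Without an SD the sample size cannot be reproduced; only the implied SD of change can be recovered. By the normal approximation it is 6.5 / [(1.960 + 0.842) × √(2/16)] = 6.56. Solving with the t distribution gives 6.35.

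**Step 1, variance.** With the same SD σ at both visits, the variance per participant is 2σ²(1−ρ) for the change score and σ²(1−ρ²) for the baseline-adjusted value. The ratio, adjusted to change, is (1+ρ)/2.

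**Step 2, cost of estimating the slope.** With 16 per arm the expected variance inflation is 1 + 1/(2×16 − 4) = 1.036, and the degrees of freedom fall from 30 to 29.

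**Step 3, power.** The simulation used 20,000 trials per value of ρ.

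| Assumed ρ | (1+ρ)/2 | Adjusted, normal approximation | Adjusted, t with slope cost | Simulated: change score / adjusted |
|---|---|---|---|---|
| 0.3 | 0.65 | 93.5% | 92.6% | 80.1% / 92.5% |
| 0.5 | 0.75 | 89.9% | 88.8% | 79.6% / 88.5% |
| 0.7 | 0.85 | 86.0% | 84.7% | 80.3% / 84.7% |
| 0.9 | 0.95 | 82.0% | 80.5% | 80.2% / 81.1% |
| 0.95 | 0.975 | 81.0% | 79.5% | 79.6% / 79.3% |

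The variance gain is cancelled where (1+ρ)/2 × 1.036 = 1, that is at ρ of about 0.93.

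**Step 4, unequal variances.** If the week-6 SD is k times the baseline SD, the ratio is k²(1−ρ²)/(1 + k² − 2ρk). For an assumed k = 1.3:
- ρ = 0.5: 1.69 × 0.75 / (2.69 − 1.30) = 0.91, or 0.94 after multiplying by 1.036.
- ρ = 0.7: 1.69 × 0.51 / (2.69 − 1.82) = 0.99, or 1.03 after multiplying by 1.036, so nothing is gained.

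**Step 5, chance imbalance.** Given an observed baseline difference D and equal variances, the change-score estimate is shifted by −(1−ρ)D: half of D at ρ = 0.5 and 30% of it at ρ = 0.7. The standard error of D is √(2/16) = 0.35 baseline SDs. As an illustration, take the implied SD of change of 6.35. At ρ = 0.5 the baseline SD is 6.35 / √(2 × 0.5) = 6.35, so an imbalance of one standard error is about 2.2 points. It moves the estimate by about 1.1 points, or 1.1/6.5 = 17% of the target difference.

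**The case against.** The strongest reply is that nothing here is an error. Participants are individually randomised, the comparison of changes is unbiased, and the sample size also rests on change scores, so design and analysis agree. That stands. A reader might infer from the regression-to-the-mean argument that the planned estimate is biased or the test invalid; the article gives no support for that. The shift in step 5 is conditional on the imbalance that happens to occur and averages to zero over randomisations.

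A reader might also infer that any baseline imbalance passes in full into the estimate. It does not; only the fraction 1−ρ does, under equal variances.

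The size of the gain is also open to challenge. No ρ is documented. The 80% starting power rests on an unstated SD and on the Short IBDQ (section 2.4), while the primary outcome is the 32-item questionnaire (section 3.2.1), so the absolute power figures are illustrative. Equal variances may fail as well. Eligibility limits disease activity at entry (section 2.2: mild to moderate activity "will be given a Mayo Clinic Score between 3–10"), and nothing limits it at week 6. That Mayo range also says nothing direct about the spread of IBDQ scores at baseline. These limits stand and are why a range is shown.

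It might be said that an analysis plan could still add covariates. That carries less weight, because section 3.4 already names the outcome form, the fixed and random terms and the reported estimate.

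Finally, nothing in the article says that the baseline comparisons replace adjustment, and means with SDs are already planned. Dropping the tests is good practice but would not change the primary estimate.

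**Conclusion.** The point holds as one of precision and of sensitivity to chance imbalance, not of validity. With 16 evaluable per arm, equal variances and an assumed 80% power for the change-score test, baseline adjustment raises power to about 93%, 89%, 85% and 81% at ρ of 0.3, 0.5, 0.7 and 0.9. With a week-6 SD 1.3 times the baseline SD, the variance ratio before the slope cost is only 0.91 at ρ = 0.5 and 0.99 at ρ = 0.7.

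Two stronger readings go too far. Adjustment is not entirely free, because a slope must be estimated from about 32 participants. And the point does not reach every analysis in the article: section 3.2.2 assigns PERMANOVA, Maaslin2 and MixOmics to the microbiome data, and a baseline-covariate model reporting an adjusted mean difference does not carry over to those.

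Confidence is high about what section 3.4 specifies and about the direction of the effect, and lower about its size, which depends on ρ and on the ratio of the two SDs.

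**What to change.** Amend section 3.4 before unblinding. For the IBDQ, the other continuous questionnaire scores, calprotectin and the serum cytokines, fit the week-6 value (or the change) on group with the baseline value of the same outcome as a covariate. The treatment estimate is the same for either form, because subtracting the baseline alters only the baseline slope, by 1. Report the adjusted mean difference with its 95% CI as the main result. Leave the PERMANOVA, Maaslin2 and MixOmics analyses as they are. Present baseline characteristics descriptively by arm, without significance tests.

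No extra participants, visits or measurements are needed. The price is one degree of freedom and about 3.6% variance inflation, with no useful gain if ρ is above about 0.9.
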